### Interventions

The effectiveness of the stepped intervention will be compared with a low-intensity intervention (one time male-specific counseling+facility navigation defined as escort to the facility (if desired) and orientation to the ART clinic and procedures) and with a high-intensity intervention (outside-facility ART initiation+male-specific counselling+facility navigation for follow-up ART visits). Across all arms, men who do not (re)initiate ART will continue receiving follow-up visits for up to 3 months, depending on preferences of the client. The number of intervention visits delivered for each participant will be documented.

#### Arm 1: low-intensity arm: male-specific counseling+facility navigation

Participants randomised to the low-intensity arm will be traced in the community and receive a one-time, one-on-one male-specific counselling session, using client-centred service techniques.^33^ All counselling sessions will be completed by a lay cadre male HIV counsellor (called Treatment Supporter in Malawi) trained in the study counselling curriculum. Treatment Supporters are responsible for routine tracing, linkage support medical record documentation and counselling.

The male-specific curriculum is developed specifically for this trial. Ministry of Health counselling materials are adapted to meet the specific needs of men, based on formative in-depth interviews, focus group discussions and a systematic literature review. Adaptations will include exploring topics of most concern to men in Malawi (ie, earning money while HIV positive, side effects and concerns regarding lifelong medication, ART as a tool to provide and care for family, etc). The materials will also include language and pictures that resonate with men (ie, emphasising how HIV and HIV services interact with men’s strength, responsibility, planning for the future), and male-specific case studies of challenges men face and how they overcome them. The adapted male-specific counselling curriculum will be developed into a standardised counselling flip chart (ie, job aid).

Men who wish to (re)initiate ART will be offered facility navigation and facility-based services. Participants will be escorted to the facility (if desired), orientated to the ART clinic procedures and introduced to other HCWs who routinely work at the facility. Facility navigation is intended to facilitate a positive experience for men by helping them feel comfortable and confident navigating clinic spaces. Men may access all ART clinical services at the health facility (but counselling described above will be provided in the community). The client will be responsible for all transport costs related to return to the facility in all study arms.

Participants who do not (re)initiate care within 14 days will be offered follow-up counselling every 2 weeks (up to 3 times) until participants (re)initiate care or inform the counsellor that they do not wish to be contacted.

#### Arm 2: high-intensity arm: male-specific counselling+outside-facility ART initiation+facility navigation

Participants in the high-intensity arm will be offered community-based male-specific counselling by HIV counsellors (described above), and offered ART (re)initiation outside facility (either at home or another location in the community of their choice). Those who choose outside-facility ART initiation will be referred to a male study nurse who will meet participants one on one at times and locations that are convenient for participants. The nurse will offer a brief counselling session, reviewing key topics from male-specific counselling curriculum that are most relevant to the individual participant. Nurses will then conduct WHO staging. Individuals classified as WHO stage 3 or 4 will be referred (and escorted, if desired) to the nearest public health facility for additional services. Participants classified as WHO stage 1 or 2 will be given same-day ART. At their 4-week follow-up ART appointment, participants will receive facility navigation by the same nurse and afterward access ART services.

Participants who choose facility-based ART (re)initiation will be referred (and escorted, if desired) by the HIV counsellor (lay cadre) to the nearest facility of their choice and receive facility navigation on a day and time that is convenient for them.

Men who do not (re)initiate care will be offered biweekly follow-up counselling at times and intervals determined by participants’ preferences until they engage in care or inform the nurse that they no longer wish to be contacted.

#### Arm 3: stepped arm

The stepped arm will build in intensity over time for those who have not (re)initiated care 14 days after study enrolment, or who do not return for their first ART follow-up appointment after (re)initiation (see figure 1). Individuals will move to the next ‘step’ every 2 weeks, moving from the lightest to the most intensive interventions over the course of 6 weeks until (re)initiation has been achieved or they inform the counsellor they do not wish to be contacted. The stepped arm includes the following steps:

##### Step 1: male-specific counselling+facility navigation and facility-based ART services

Step 1 includes the same components described in the low-intensity arm. Briefly, participants will be traced in the community and receive a one-time male-specific counselling session. Men who wish to (re)initiate care will be provided facility navigation and standard of care facility-based services.

**Figure 1 F1:**
[figure not shown]
Trial design. ART, antiretroviral therapy.

##### Step 2: ongoing motivational interviewing+facility navigation and facility-based ART services

Men who do not (re)initiate care (either have not engaged ART within 14 days of enrolment or do (re)initiate ART but are >7 days late for a follow-up appointment) will move to the next ‘step’ of the intervention, which adds ongoing motivational interviewing to their package of activities. Motivational interviewing is a client-centred, client-led method for counselling that helps participants identify barriers to a desired outcome and develop personalised solutions.^34 35^ The strategy has successfully been used with ART clients.^36^ Mentors will work with participants to: (1) build self-efficacy, (2) identify internal motivations for the desired behaviour, and (3) establish strategies and short-term and long-term goals needed to reach ART initiation and retention. A male mentor specifically trained in motivational interviewing adapted to the local context and male population will provide ongoing, one-on-one in-depth counselling, motivational interviewing and general ‘check-ins’ approximately twice within a 2-week period. The mentor will not necessarily be HIV positive (unlike other mentorship models) as the Malawi Ministry of Health has moved away from HIV-positive peer mentor cadres. However, they will be experienced in HIV counselling and trained in male-specific needs. Motivational interviewing will take place in a location preferred by the participant, likely in the community. Participants who choose to (re)initiate ART can access ART services at the facility of their choice and will be given facility navigation as described in arm 1.

##### Step 3: outside-facility ART initiation+male-specific counselling

Men who are not engaged after step 2 (either have not (re)initiated ART <14 days after moving to step 2 or did (re)initiate but are >7 days late for a follow-up ART appointment) will be offered outside-facility ART by a male nurse certified in HIV counselling. Steps will follow those outlined in the high-intensity arm, with a brief counselling session, WHO staging, same-day ART reinitiation for those WHO stage 1 or 2, and facility navigation for their 4-week follow-up appointment.

### Trial setting

The study will take place in central and southern Malawi. Malawi has an HIV prevalence of 9.6%,^37^ and of the estimated 330 000 men living with HIV in the country, 54 500 are not in care.^38^ Men in Malawi live in primarily rural settings, are self-employed and subsistence farmers; the minority have regular access to a private phone and most are highly mobile.^39 40^

### Population

We will recruit men from 13 high-burden health facilities in Malawi, using medical chart reviews to identify men living with HIV who are not engaged in HIV care. Study facilities will vary by facility type (hospital/health centre), management (public/mission), location (rural/urban) and region (central/southern Malawi).

Eligibility criteria for men include: (1) ≥15 years of age; (2) live in facility catchment area; and (3) tested HIV positive and either (a) self-report having not yet initiated ART within 7 days of testing HIV positive, (b) initiated ART but are at risk of immediate default (ie, ≥7 days late for their 4-week ART refill appointment), or (c) initiated ART and attended their first refill appointment but later defaulted (ie, >28 days late to care). For those who never initiated ART and do not have proof of a confirmatory HIV test, study staff will offer an HIV self-test kit prior to enrolment, to confirm a positive HIV status. Those who choose to initiate ART will receive the standard Determine and Unigold confirmatory tests prior to ART initiation, following routine care.

### Study outcomes

The primary outcome is the proportion of men who are retained in ART care 6 months after (re-)engagement. Secondary outcomes include: (1) ART initiation; (2) adverse events experienced by men or their female partners (ie, unwanted disclosure, end of relationship or IPV; (3) intervention acceptability and (4) cost-effectiveness. ART retention outcomes will be measured through medical chart reviews, while secondary outcomes will be measured through self-reports. Process outcomes include: (1) the proportion of men who were successfully traced; (2) the proportion of eligible men who consented to participate; (3) men’s experience with the intervention and (4) the quality of the intervention.

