## Methods and analysis

### Objectives

Our primary objective is to test the effect of a male-specific, stepped intervention on men’s 6-month retention in ART care compared with male-specific low-intensity and high-intensity interventions (retention is defined as <28 days late for their 6-month ART appointment). Secondary objectives are to understand the effect of a stepped intervention on: (1) ART initiation; (2) the presence of adverse events (ie, unwanted disclosure, end of relationship or intimate partner violence (IPV)); (3) intervention acceptability and (4) cost-effectiveness.

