#### Follow-up data

Study staff will administer follow-up surveys at 2 and 4 months after enrolment. Follow-up surveys will measure exposure to (and acceptability of) the interventions, changes in key demographics since enrolment (ie, marital status, number of children, employment, self-rated health), any adverse events since enrolment (ie, unwanted status disclosure, termination of relationship due to the intervention) and use of ART services. The location and specific time of the follow-up survey will be based on participant preference.

Medical chart reviews will be conducted to assess men’s engagement with ART services 6 months after study enrolment. Individuals without a medical chart outcome will be followed up in person and their health passport, a pocket medical record where providers record data during health visits, will be reviewed to collect the ART outcome. Men who cannot be reached or are lost to follow-up in any arm will be counted as failures for that specific ART outcome of interest: (re)initiation or 6-month retention.

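### The primary outcome has two conflicting time origins, 6 months from (re-)engagement and 6 months from enrolment, and the gap between them depends on arm

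*Protocol article*

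**What the plan says.** Three places in the protocol article bear on when the primary outcome is measured.

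- Study outcomes: "The primary outcome is the proportion of men who are retained in ART care 6 months after (re-)engagement".
- Follow-up data: "Medical chart reviews will be conducted to assess men’s engagement with ART services 6 months after study enrolment". The same paragraph then applies its failure rule to both (re)initiation and 6-month retention, so it does concern the primary outcome.
- Objectives: "retention is defined as <28 days late for their 6-month ART appointment". No starting point for the 6 months is given.

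The Abstract, Sample size considerations and Analysis plan do not settle the origin. The data source is fixed ("ART retention outcomes will be measured through medical chart reviews, while secondary outcomes will be measured through self-reports"), with an undated fallback: "Individuals without a medical chart outcome will be followed up in person and their health passport" is then reviewed.

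The time from enrolment to (re-)engagement varies by design. In the high-intensity arm, at the nurse visit, "Participants classified as WHO stage 1 or 2 will be given same-day ART". In the stepped arm, "Individuals will move to the next ‘step’ every 2 weeks, moving from the lightest to the most intensive interventions over the course of 6 weeks", and outside-facility ART is offered only at step 3. In all arms, "men who do not (re)initiate ART will continue receiving follow-up visits for up to 3 months".

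**The concern.** (Re-)engagement is a post-randomisation event that the interventions are meant to influence. A clock that starts there begins at a different point for each man, and on average perhaps at a different point for each arm. A clock that starts at enrolment is common to all men, but a late starter then has less time on ART in which to drop out before he is assessed. These are two different estimands, and the protocol describes both as the primary outcome.

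Take a man who starts ART at week 6, is in care 6 months after enrolment and has left care a month later. He can be a success under Follow-up data and a failure under Study outcomes. Such men should be more common where initiation is slower by design, so the choice of clock can move the stepped versus high-intensity contrast. It may also move stepped versus low-intensity, but the direction there is unclear, because step 1 is the low-intensity package.

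The (re-)engagement clock has a further ambiguity. The stepped arm escalates men who (re)initiate and then become more than 7 days late, and the Population section admits men who had already started ART. More than one engagement could therefore start the clock.

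The trial is non-blinded. An unresolved primary definition leaves room to choose once results by arm can be seen.

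**Working it through.** **1. The plan's own figure.** Inputs from Sample size considerations: 181 men per arm; retention 40%, 60% and 80%; 20% loss, with lost men counted as failures; test level 0.025 (taken as two-sided); asymptotic normality of the log OR. Multiplying by 0.8 gives 32%, 48% and 64%.

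SE = sqrt(1/(n·p1·q1) + 1/(n·p2·q2)); power = Φ(|log OR|/SE − 2.241).

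- Stepped v low: log OR 0.674, SE 0.218, power 0.802.
- Stepped v high: log OR 0.655, SE 0.215, power 0.791.

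The stated 0.8 is reproduced. No time origin enters this calculation, so the conflict does not change it.

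**2. Dates.** Take 6 months as about 183 days. Under Study outcomes and Objectives together, the lateness allowance ends at (re-)engagement day + 183 + 28. The (re-)engagement days below are illustrations from the step schedule and the 3-month limit on follow-up visits.

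| (Re-)engagement, day after enrolment | 6-month appointment, day | Allowance ends, day | Day 183 is early by | Months since (re-)engagement at day 183 |
|---|---|---|---|---|
| 0 | 183 | 211 | 28 days | 6.0 |
| 14 | 197 | 225 | 42 days | 5.5 |
| 28 | 211 | 239 | 56 days | 5.1 |
| 42 | 225 | 253 | 70 days | 4.6 |
| 91 | 274 | 302 | 119 days | 3.0 |

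A status read at exactly 6 months from enrolment comes before the allowance ends for every man who (re)engages at or after enrolment. For those who do so after enrolment, it also comes before the 6-month appointment itself.

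**3. Size per late starter.** The Introduction gives repeat interruption within 6 months as 30% to 40% of returners (q). Assume a constant hazard λ = −ln(1 − q)/6 per month: 0.0594 for q = 0.30 and 0.0851 for q = 0.40. A man starting d months after enrolment is retained at 6 months from enrolment with probability exp(−λ(6 − d)). At 6 months from his own start the probability is 1 − q.

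| Delay d | q = 0.30 | q = 0.40 | Excess on enrolment clock |
|---|---|---|---|
| 0.5 month (about 2 weeks) | 0.721 v 0.700 | 0.626 v 0.600 | 2.1 to 2.6 points |
| 1.5 months (about 6 weeks) | 0.765 v 0.700 | 0.682 v 0.600 | 6.5 to 8.2 points |
| 3 months (about 13 weeks) | 0.837 v 0.700 | 0.775 v 0.600 | 13.7 to 17.5 points |

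Delays are rounded to half-months. Taking 6 weeks exactly (42/30.44 = 1.38 months) gives 6.0 to 7.5 points.

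**4. Size at arm level.** The shift in an arm's proportion is the share of randomised men who start late multiplied by the per-man excess. The protocol gives no such shares. If 25% to 50% of an arm started at about 6 weeks (an assumption), the shift is 0.25 × 6.5 = 1.6 to 0.50 × 8.2 = 4.1 points. The effect on a contrast is the difference between two such shifts.

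**The case against.** The best defence is that Follow-up data can be read as naming the date of the status to be assessed, not the day on which the chart is pulled. No abstraction date is fixed, and a later review or the health-passport check could cover the 28-day allowance. That reading is fair, and it answers part of the timing problem. It does not answer the conflict, because a status date 6 months after enrolment is still the enrolment clock and still disagrees with Study outcomes.

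Several stronger readings are tempting and are not supported.

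- *The outcome cannot be observed in any man at 6 months from enrolment.* A man who (re)initiates at enrolment and attends his 6-month appointment on time or early is visibly retained. What cannot yet be established is the failure of a man who is late.
- *Men who never engage have no defined outcome.* Sample size considerations describes success as engaging and being retained, Follow-up data counts lost men as failures, and the Analysis plan includes all randomised men. A man who never engages is simply not retained.
- *The 14-18 points can be set against the planned 20-point difference* (16 after loss). The former is per late-starting man under an assumed hazard; the latter is a difference between arms. Moreover, the 3-month limit applies to every arm and so is not differential in itself.
- *The last outcomes fall within about 10 months of enrolment.* Three months limits intervention contacts, not (re)initiation, so no such bound follows.

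**Conclusion.** The conflict stands and should be resolved before outcomes are analysed. It is a contradiction in the definition of the primary endpoint, not detail left to a fuller document. The two clocks can code the same man differently, and the lag that separates them depends on arm by design.

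The size at arm level is uncertain. The per-man excess of about 2-3, 7-8 or 14-18 points rests on a constant hazard and on a background figure for repeat interruption, which is not the same as status under the 28-day rule. The arm-level shift is smaller, at about 1.6 to 4.1 points under the shares assumed above. Sample size and power are unaffected.

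A reader might infer that one clock is biased and the other is not. The documents do not support that. Timing from randomisation keeps the shorter time on ART of late starters. The case for it is that it gives every man the same time zero, in line with the planned intention-to-treat analysis.

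**What to change.** State one time origin, in the same words, under Objectives, Study outcomes and Follow-up data.

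**Preferred: randomisation.** Success means having (re)initiated ART and being less than 28 days late for the ART appointment that applies at 6 months after randomisation. Keep all randomised men in the denominator, with never-initiators and lost men as failures. Ascertain status only once 6 months plus 28 days have passed. Say openly that late initiators then have less time on ART. Report retention 6 months after (re)initiation as a supportive analysis.

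**If the (re-)engagement clock is kept:** state which (re-)engagement starts it, keep the same denominator and failure rule, and time each man's chart review at (re)initiation plus 6 months plus 28 days.

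**Cost:** a wording amendment and chart abstraction about one month later, or longer for late initiators if the (re-)engagement clock is kept. No additional participants are needed.

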#### Sample size considerations

We powered the study to detect differences in 6-month retention between stepped and low-intensity arms, and the stepped and high-intensity arms. Based on pilot data, we assumed that 40% of men in the low-intensity arm, 60% in the stepped arm and 80% in the high-intensity arm will engage in ART and be retained at 6 months. Any man lost to follow-up will be treated as a failure for the outcome evaluation. With 181 men per arm and 20% loss to follow-up from the study in all arms, the power for detecting the specified differences between stepped and low-intensity arms and between stepped and high-intensity arms will be 0.8, with test level 0.025 after Bonferroni adjustment for two comparisons. We will have 0.99 power to detect specified differences between low-intensity and high-intensity arms. The calculation is based on asymptotic normality of log OR.^41^ We need to enrol and randomise 181 men per arm (a total of 543 men living with HIV).

### Data collection

Study recruitment, enrolment and data collection will be conducted by male study staff, who are distinct from local HCWs implementing the interventions.

#### Recruitment

Men will be identified through both medical register reviews and in-person recruitment at participating health facilities. Various medical charts will be reviewed to identify different types of eligible men: HIV testing and counselling and ART registers to identify men who tested HIV positive but never initiated ART; client follow-up registers to identify those who initiated but never returned for their first ART appointment or those who defaulted from care; and index counselling and testing registers to identify male partners of female ART clients (figure 2). In-person recruitment will involve screening men at outpatient departments (OPDs) because our previous research has found that men in Malawi frequent OPD settings for health needs,^17^ and our formative work suggests that men who disengage from ART services still frequent the OPD for care. In-person recruitment will be used for all client types.

**Figure 2 F2:**
[figure not shown]
Recruitment sources and ART disengagement criteria by recruitment type. ART, antiretroviral therapy.

#### Tracing and eligibility screening

Study staff will trace potential participants identified through medical chart reviews via phone (if available) or home visits based on tracing data provided in medical documentation. All potential participants will be traced up to three times before being considered lost to follow-up. All screening and enrolment processes will take place in person.

#### Consent, enrolment and baseline survey

Men who are eligible for the study will complete written informed consent and complete a baseline survey immediately following enrolment. The baseline survey will collect data on key demographic variables (marital status, number of children, employment, self-rated health) and previous engagement with HIV and non-HIV health services. All surveys will be conducted in the local language (Chichewa) by trained study staff using electronic tablets. Surveys will be programmed using SurveyCTO software (http://www.surveycto.com).

